#### Secondary hypothesis on overall malaria infection

The sample size calculated to yield 85% power for establishing the primary hypothesis on first-time infection PE also leads to at least 85% power when it comes to the testing of the secondary hypothesis on the overall malaria infection. This is because that the baseline overall malaria incidence rate is likely to be no lower than 3.0 per person-year (the first-time incidence rate), and there is no interim analysis on the second hypothesis.

#### Quantification of diversionary effect

Since there is no formal hypothesis on the SR-diversion objective, we focus on determining a practically feasible sample size that will give a relatively high precision for the estimated PE of SR in the cluster buffer zone on the malaria incidence rate. With a 44% between-cluster CV, and a baseline incidence rate of 3.0 per person-year, 30 clusters per arm with 28 subjects (HHs) per cluster leads to a half width of 0.220 for the 90% confidence interval on the log scale, or the ratio between the upper bound of the 90% confidence interval versus the point estimate is 1.245 for a hazard ratio estimate between SR and placebo buffer zone subjects (HHs). Factoring in a 35% LTFU rate, the required sample size is 40 subjects (HHs) in the buffer zone per cluster. The total subjects (HHs) will be split in half between two sequential cohorts (cohort 1 and cohort 2), with 20 subjects (HHs) per cohort per cluster.

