#### Primary hypothesis on first-time malaria infection

The sample size determination on the required number of subjects (HHs) per cluster for testing the primary hypothesis is based on the hazard rate comparison in the proportional hazards regression model [36, 37]. With the following specifications: 1-sided type I error rate = 5%, true PE = 30%, a between-cluster CV of hazard rate = 44% (based on historical data collected from Kenya), one interim analysis for efficacy and non-binding futility with the O’Brien-Fleming error spending function when 50% of events have been collected then 1055 first-time malaria events will need to be observed to reach 85% power in testing the primary hypothesis on PE.

With a baseline first-time malaria infection hazard rate of 3.0 per person-year, 30 clusters per treatment arm, with 20 subjects (HHs) per cluster are expected to yield 1055 independent first-time malaria events within a 12-month follow-up period per cohort post randomization to yield 85% power. If, by the end of the 2-year study, 1055 independent malaria events are not reached, the study may extend until 1055 events are collected without inflating the type I error rate in the testing of the primary hypothesis. Factoring in a LTFU rate at 35%, the required sample size is 28 subjects (HHs) per cluster, which will be split in half between the two sequential cohorts with 14 subjects (HHs) per cohort per cluster.

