## Statistical methods

### Statistical methods for primary and secondary outcomes {20a}

#### Primary hypothesis

H_0_: SR does not reduce the first-time malaria hazard rate compared to placebo in Kenya.

H_1_: SR reduces the first-time malaria hazard rate compared to placebo (first-time malaria hazard ratio between SR and placebo is < 1; the expected hazard ratio is 70% or PE is 30%.

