### Interim analyses {21b}

There will be one formal interim analysis to test the primary hypothesis. The decision boundaries at the interim analysis are calculated for either stopping for futility or stopping for efficacy using the O’Brien-Fleming error spending function [36, 38–41]. Since we adopt the non-binding futility boundary [42, 43], if it is decided the study will continue due to other considerations even if we cross the futility boundary at the interim look, there will be no inflation of type I error. In other words, the trial does not need to stop to accept the null hypothesis when the test statistic falls in the futility region at the interim stage. In addition, since trials submitted to VCAG are intended to demonstrate public health value, the committee strongly recommends trials are not stopped early for benefit. In our design setting, even if the efficacy boundary is crossed at the interim look, the study may continue and there will be no inflation of type I error, as efficacy is already established at the interim. The interim analysis will occur when 528 events (50% information) are collected.

If the interim result meets the stopping criterion for futility, that is, the one-sided *p*-value for Wald’s test on the log(HR) between SR and placebo at the interim is > 0.3450, the study may stop for futility. Since we adopt the non-binding futility boundary, if it is decided the study will continue due to other considerations even if we cross the futility boundary at the interim look, there will be no inflation of type I error. If the one-sided *p*-value < 0.00882, then the study can stop for efficacy; otherwise, the study will proceed. However, if it is decided the study will continue due to other considerations even if we cross the efficacy boundary at the interim look, there will be no inflation of type I error, as efficacy is already established at the interim.

If the one-sided *p*-value at the interim is > 0.00882 but < 0.3450, then the study will continue. At the final analysis, if the one-sided *p*-value from Wald’s test on the log(HR) between SR and placebo < 0.04668, we will reject the null hypothesis, claiming SR reduces the malaria hazard rate compared to placebo in Kenya at the significance level of 5%; otherwise, we will fail to reject the null hypothesis, claiming SR does not reduce the malaria hazard rate compared to placebo in Kenya.

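### The buffer-zone precision (90% half-width 0.220 at 28 children per cluster) does not fit the primary power (85% at 20 per cluster), although both use the same CV, rate and number of clusters

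*Protocol article*

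**What the plan says.** Both calculations stand under Sample size {14} of the protocol article.

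- **Primary hypothesis on first-time malaria infection.** The specification is "1-sided type I error rate = 5%, true PE = 30" percent and "a between-cluster CV of hazard rate = 44" percent, with one interim look. The conclusion is that "1055 first-time malaria events will need to be observed to reach 85% power in testing the primary hypothesis on PE". The rate and cluster inputs read "With a baseline first-time malaria infection hazard rate of 3.0 per person-year, 30 clusters per treatment arm". For the expected yield, the same sentence goes on to say that these clusters "with 20 subjects (HHs) per cluster are expected to yield 1055 independent first-time malaria events within a 12-month follow-up period". The 20 is the evaluable number; it becomes 28 after allowance for 35% loss to follow-up.
- **Quantification of diversionary effect.** With the same CV and rate, "30 clusters per arm with 28 subjects (HHs) per cluster leads to a half width of 0.220 for the 90% confidence interval on the log" hazard ratio, also given as a ratio of 1.245. The 28 is again the evaluable number; it becomes 40 after the same loss allowance.

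Interim analyses {21b} gives the decision rule: one look at 528 events, efficacy at one-sided p < 0.00882, non-binding futility at p > 0.3450, and success at the end "if the one-sided *p*-value from Wald’s test on the log(HR) between SR and placebo < 0.04668".

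**The concern.** The two calculations share the number of clusters, the CV and the rate. A one-sided 5% test and a two-sided 90% interval also use the same normal quantile. The only stated design difference is the number of evaluable children per cluster: 20 for the primary, 28 for the buffer zone. The Cohort follow-up section says that buffer-zone children are followed by the same procedures, and no other CV, model or follow-up time is given for them. More children per cluster should give a narrower interval, but the buffer-zone interval is wider than the primary power claim allows.

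The half-width is the only numerical support given for recruiting 40 children per cluster in the buffer zone (40 × 60 = 2400 over two cohorts). The article also plans to revisit the assumptions after baseline and possibly adjust the sample size, and that needs one coherent variance model.

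**Working it through.** **Inputs.** HR 0.70, so |log HR| = 0.3567; 30 clusters per arm; CV 0.44; rate 3.0 per person-year; 1055 events; boundaries 0.00882 / 0.3450 / 0.04668 at 50% information. Ignoring futility, these boundaries give an overall one-sided error of 5.00%.

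**1. Reproduce the primary figure.** The article prints no variance formula, so I assume the usual one:

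Var(log HR) = 2·CV²/30 + 4/events.

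- Cluster term: 2 × 0.1936/30 = 0.01291. Event term: 4/1055 = 0.00379. SE = √0.01670 = 0.1292, half-width 1.645 × 0.1292 = 0.2126.
- Drift 0.3567/0.1292 = 2.76. Power under the stated boundaries is 84.3% with futility followed and 86.3% with it ignored. (With the cluster term also in the interim variance, the information fraction is about 0.81 and power with futility followed is 86.1%.)

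The stated 85% is reproduced.

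**2. What 85% power requires at 20 per cluster, whatever the variance formula.**

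| Rule | Drift needed | SE at most | 90% half-width at most |
|---|---|---|---|
| Stated boundaries, futility followed | 2.792 | 0.1278 | 0.210 |
| Stated boundaries, futility ignored | 2.701 | 0.1320 | 0.217 |
| Fixed design, no interim look | 2.681 | 0.1330 | 0.219 |

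Each limit, for 20 children, is already below the 0.220 printed for 28.

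**3. Move from 20 to 28 per cluster.** Expected events among 28 × 60 = 1680 children:

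- at the primary section's own yield (1055/1200 = 87.9%): 1477
- at 1 − exp(−3) = 95.0% in both arms: 1596
- at 95.0% on placebo and 1 − exp(−2.1) = 87.8% on SR: 1535

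Taking the saved event variance (4/1055 − 4/1477 = 0.00108, or 4/1055 − 4/1596 = 0.00129) off the limits in step 2 gives half-widths of at most 0.202–0.203 (futility followed) or 0.209–0.210 (ignored).

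**4. Buffer zone with the formula of step 1.**

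| Events | SE | Half-width | Ratio |
|---|---|---|---|
| 1477 | 0.1250 | 0.2055 | 1.228 |
| 1535 | 0.1245 | 0.2049 | 1.227 |
| 1596 | 0.1241 | 0.2042 | 1.227 |

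The printed values are 0.220 and 1.245. That exp(0.220) is 1.246 rather than 1.245 is only rounding.

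**5. Reverse check: suppose 0.220 at 28 is right.** SE = 0.220/1.645 = 0.1338, variance 0.01789. Less 4/1596 = 0.00251, this leaves a cluster term of 0.01538, an effective CV of √(15 × 0.01538) = 48%. Adding back 4/1055 gives SE 0.1385 for the primary and power of 79.7% (futility followed) or 81.9% (ignored). With 1477 events the results are 80.0% and 82.3%.

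**The case against.** The strongest reply is that the conflict nearly vanishes unless a variance formula is assumed. Against a fixed design the gap is 0.219 versus 0.220, and the printed ratio of 1.245 corresponds to 0.2191. The methods are left to cited references. Other variance choices also come closer:

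- **t quantile on 58 df (1.672).** Then 0.220 means SE 0.1316, just inside the 0.1320 limit for 20 children. But the children now number 28, and after the move in step 3 the t-based half-width is at most about 0.214.
- **Design effect 1 + (m − 1)CV².** At 28 per cluster this gives 0.2055 (1596 events) to 0.214 (1477 events). It puts the primary power at 82–84% under the stated boundaries, not 85%.
- **Gamma cluster frailty analysed on the log scale.** Simulation gave 0.213–0.219 at 28, and a t quantile would bring 0.220 within range. Primary power is then about 82% (84% with futility ignored).

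So no variant tried gives both printed figures under the stated boundaries. What stands is that the replacement value depends on a formula the article does not print.

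A reader might infer that 0.220 was computed for one cohort of 14 per cluster, since the step 1 formula gives 0.2202 there. That needs a 95% event yield (798 of 840). At the primary section's own 87.9% it gives 0.223. The design-effect form with 20 per cluster and 1055 events gives 0.2191, a ratio of exactly 1.245, so a rival origin fits at least as well. The document does not settle it.

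A reader might also infer that the trial is underpowered. The document does not support this: the 85% is reproduced from its own inputs, and the lower power follows only if 0.220 is confirmed.

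Finally, the article describes the buffer sample as a matter of feasibility as well as precision, and sets no formal diversion hypothesis. Both points are fair and limit the weight of the finding.

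**Conclusion.** The concern holds as an inconsistency between two stated figures. With shared clusters, CV and rate, 85% power at 20 per cluster implies a half-width of about 0.20–0.21 at 28, against 0.220 as printed. Under the usual formula the ratio is about 1.23 rather than 1.245. The half-width is the more likely of the two to be wrong, because the primary power is reproduced and the half-width is not.

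This rests on the buffer-zone endpoint, follow-up and cluster variation matching the primary, as the article implies, and on 28 being the evaluable number, which its loss allowance shows. The source of 0.220 is unknown, and the exact replacement depends on the variance form.

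The consequence is modest. If the primary figure is right, the diversion estimate will be somewhat more precise than promised, and no test or boundary changes. Only if 0.220 is confirmed does the primary power claim fall, by about 3 to 5 points.

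**What to change.** Recompute both figures with one stated variance formula and one stated event yield, and restate the one that changes.

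- If the 85% power is kept, replace 0.220 and 1.245 with about 0.205 and 1.23 (up to about 0.214 and 1.24 under other variance forms).
- If 0.220 at 28 per cluster is confirmed, restate the primary power as about 80–82%.
- If the buffer-zone figure used a different assumption, state that assumption. Do not relabel 0.220 as the value for 14 per cluster without the original calculation.

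The cost is one recalculation and a wording change in the sample-size section. Enrolment and conduct are unaffected.

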### Recruitment {15}

Information will be distributed through Community Interviewers (CIs) and community health workers, and other study staff, targeting parent(s)/guardian(s) of potential participants in the community. Fliers or posters will be developed and information will be provided through the following means: Community meetings in facilitation with local Chiefs Barazas, church meetings where recruitment scripts will be read and fliers handed to the parent(s)/guardian(s) of potential participants and discussions with church members; attendance at established local community advisory board (CAB) and opinion leaders’ meetings, women groups, and men groups.

After community entry, a list of all chief barazas, CAB meetings, Community Health Volunteers (CHVs), and community gatherings for a particular month will be prepared. The component leads, in consultation with the study coordinator and community interviewers, will organize to attend the meetings to share information about the study and plan a schedule for recruitment. If no meetings are planned during specific month when recruitment is ongoing, the study coordinator will organize meetings as needed. The recruitment team that includes the study clinician, community interviewers, and CHVs will set up one or several tents in strategic places and meet parents of potential participants. Should the community offer to use rooms in a school or church, especially during the rainy season, this will be accepted, as this will be mainly for sensitization activities. The study mobile field sites will be set up in 1 to 4 sub-locations at a given time with the guidance of the CHVs and all interested parents/legally acceptable representatives with potential participants in that area will be invited for information about the study.

Within each cluster, individual compounds will be enumerated and then randomly selected for inclusion in each cohort (baseline, cohort 1, cohort 2). Parents with children aged ≥ 6 months to 9 years 11 months will be eligible for consenting into participation in the SR study. Community interviewers will also trace pre-selected compounds where they will obtain verbal consent from head of HHs to collect baseline information which includes listing all the children between ≥ 6 months and 9 years 11 months in the compound. This master list will be used to randomly select one child per HH for subject recruitment. Compounds selected for inclusion in the baseline cohort will be eligible for inclusion in cohorts 1 or 2 after implementation of the intervention. However, those children enrolled in cohort 1 after implementation of the SR will not be eligible for enrolment in cohort 2 for the second year of follow-up.

## Assignment of interventions: Allocation

### Sequence generation {16a}

For the baseline cohort, recruitment of participants for enrolment was based on random selection of HHs using census mapping of the study area. Random allocation of clusters into treatment assignment will be performed during baseline following interim analysis of incidence and prior to cohort 1 participant enrolment. Baseline estimates of incidence will be used to guide decisions on cluster stratification. A total of 60 clusters (30 per treatment arm) will be randomly allocated to receive either the SR intervention or placebo treatment. The cluster allocation sequence will be generated by the external statistician serving on the Data Safety Monitoring Board (DSMB) using a random number generator (https://www.random.org).

### Concealment mechanism {16b}

Investigators, study biostatistician, staff, and study participants will be blinded to cluster, thus HH treatment allocation. The SR intervention and placebo will have identical design and packaging and will be deployed in houses by study personnel using a blinded coding scheme. The study biostatistician will remain blinded throughout the trial, but will conduct an unblinded analysis following database lock upon completion of all data entry and resolution of standing data queries at the end of the study.

### Implementation {16c}

The distribution of the intervention will occur after the completion of baseline phase analyses and verification of underlying assumptions on study power (incidence, CV).

All consented HHs located within cluster core areas, including those that do not have a child subject enrolled in an incidence cohort, will have product placed inside their homes at the manufacturer’s recommended application rate of 2 units per 9 m^2^ floor area. Trained study teams will be responsible for managing product implementation including initial deployment of product, subsequent removal, and replacement at 4-week intervals.

## Assignment of interventions: Blinding

### Who will be blinded {17a}

All participants, investigators, and study staff will be blinded to cluster, thus HH, allocation throughout the duration of the trial.

### Procedure for unblinding if needed {17b}

#### Non-emergency unblinding of a single participant

If, because of an AE which might be related to the SR product, and non-emergency unblinding of an individual participant is considered, unblinding will follow recommendations outlined in pre-specified standard operating procedures for non-emergency unblinding. The site clinician will inform the Site PI of the AE under consideration, and the Site Principal Investigator (PI) will contact the University of Notre Dame (UND) Lead PI and the medical monitor on the DSMB to discuss the case and obtain agreement that the participant, thus HH allocation, should be unblinded in a non-emergency manner. If unblinding is agreed upon, the sealed (digital password protected) intervention assignment will be with the Site PI but only opened by a pre-designated person external to the study (i.e., administrator) so as to maintain the Site PI’s and study staff blinding to cluster assignments. Documentation of the unblinding will be performed with a subsequent follow-up memo to the UND Lead PI, and DSMB. Reporting of non-emergency unblinding due to an AE will be conducted as prescribed by corresponding institutional review boards (IRB) by the Site PI, UND Lead PI, or designee. The possible effect of unblinding on the planned study data analysis will be determined by the Site PI or designee.

#### Emergency unblinding

Emergency unblinding will be considered in instances of a suspected unexpected SAE to the study product or procedures (malaria treatment, mosquito collection) as judged by a site physician following recommendations outlined in pre-specified standard operating procedures for emergency unblinding. The first alert will be raised by a study physician within 24 h of becoming aware of the SAE in an expedited report to the Site PI, UND Lead PI, and DSMB. Documentation of the unblinding, reporting to IRBs, and possible effects of unblinding on the planned study data analysis will follow similarly as described above.

## Data collection and management

### Plans for assessment and collection of outcomes {18a}

#### Mapping of the study area and baseline measurements

Prior to enrolment, all structures (human dwellings) in the study area will be mapped using GPS coordinates and assigned a unique identification number. A baseline questionnaire will be administered to measure HH and entomological characteristics. Profiles of enrolled HHs that could potentially confound effect on mosquitoes, thus malaria transmission, will be generated. This includes house construction materials, socioeconomic status, number of inhabitants and their age, current method(s) used to prevent mosquito bites (including ITNs), and presence of domesticated animals, density, and location. A cluster will be defined as a village which will serve as the core area where the intervention is implemented plus a buffer zone extending 300–500 m beyond the core area which will be used to estimate the diversionary effect of the intervention on epidemiological and entomological endpoints (Fig. 1) [30]. Since the buffer zones will extend into neighboring villages, an anticipated 100–150 villages will be mapped to account for buffer zones. Core areas (villages) plus their buffer zones will be identified using mapping software (ArcGIS/QGIS) based on the feasibility of identifying 60 villages plus their surrounding buffer zones.

#### Description of study clusters

The unit of randomization for the intervention will be a cluster. A total of 60 clusters will be delineated for the trial (Fig. 1). A cluster is defined as a core area, where the SR or placebo will be implemented, plus an untreated buffer zone where diversionary effects of the Mosquito Shield™ will be measured. The core areas of each cluster will be discrete villages. In the Health and Demographic Surveillance System maintained by KEMRI and CDC in neighboring Siaya County, the average village has 103 compounds in an area of 1.75 km^2^. Compounds are defined as family units with one or more structures plus surrounding farmland. A typical family compound has 5.5 HH members. Therefore, an average population size for a village in this area is estimated to be 567 inhabitants. Pre-trial census data will be used to delineate cluster boundaries based on number of HHs and inhabitant age groups such that each cluster will have at least one anticipated child meeting the inclusion criteria for assurances of sample size requirements.

For the buffer zones, mapping will extend approximately 300–500 m from the border of each cluster core area. Assuming core areas are approximately round with an area of 1.75 km^2^, this will result in a radius of 0.75 km. Extending a buffer zone 300 m around the core area will result in a radius of 1.05 km, and extending a buffer zone 500 m will result in a radius of 1.25 km. Estimating the total area including the buffer zones and then subtracting out the area of the core area results in areas of 1.7 km^2^ and 3.1 km^2^ for buffer zones of 300 m and 500 m respectively. Typically, HHs are randomly distributed in the landscape of western Kenya and it is therefore expected that a 300 m buffer zone of 1.7 km^2^ should have a similar number of HHs as the core areas which are estimated to have an area of 1.75 km^2^. Final determination of the buffer zones will be based on mapping and the actual number of HHs required to meet the sample size of 40 HHs per cluster for the analysis of SR diversionary effects. Because the buffer zones will extend into neighboring villages, we will map approximately 100–150 villages and then select villages as core areas based on feasibility of including a 300–500 m buffer around 60 of them.

